### Sample size

This is a non-inferiority trial to evaluate efficacy and the primary endpoint is Hb concentration (measured using a Medonic haematology analyser in the laboratory) at day 84. Based on a SD of 1.15 g/dL of the mean Hb value of children at 24 week of age, from a previous trial conducted at Keneba [19], a sample size of 131 participants in each of the three arms is required using a 1-sided α of 2.5 and a Bonferroni correction to adjust for multiple testing. A total sample size of 393 children followed up for 12 weeks, with a drop-out of less than 15 %, will provide 80 % power to establish that:arm B is non-inferior to arm A on the primary endpoint (Hb concentration at Day 84) defined as the upper 98.3 % confidence limit for the difference in mean Hb being not greater than 0.5 g/dL (non-inferiority margin), the smallest value considered to be of public health relevancearm C is non-inferior to arm A at the same level as abovearm C is non-inferior to arm B at the same level as above

For the sub-study, the power calculation for iron absorption is based on the data from Fomon et al. [20] in infants. Twenty subjects per group are required to resolve a difference in absorbed iron of 0.080 mg/d between the control and intervention period, based on a SD of 0.13 mg/d (paired t-test). The between group difference that we estimate being able to resolve is 0.12 mg/d absorbed iron (unpaired *t*-test). Lower variability is expected in the calculated k_abs_ values, which are independent from Hb, body weight, and iron status, the main contributors to variability in the calculation of iron absorption. Considering attrition due to the long time span of at least 7 months between recruitment (administration of stable isotope dose) and participation in the main study, 30 subjects per group will be recruited.

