### Statistical analysis

The primary haemoglobin outcome (measured using a Medonic haematology analyser in the laboratory) at day 84 will be tested for non-inferiority by performing a per-protocol analysis with a 5 % significance level, adjusted using the Bonferroni correction to account for three main comparisons. We will also repeat the main analysis using the intention-to-treat population as a confirmatory analysis.

Secondary outcome analysis of continuous variables (ferritin, sTfR, transferrin, TSAT, CRP, AGP, calprotectin, *ex-vivo* growth, gut microbiota, number of weeks supplemented) will be done using mixed-effect models with individuals treated as a random effect, and secondary outcome analysis of categorical variables (anaemia, ID and IDA) will be modelled using mixed-effect logistic regression. Interactions between study arm and time in the study will be investigated.

Morbidity data will be analysed using mixed-effect models controlled for possible confounders.

Exploratory analysis will be performed using serum iron.

All data will be analysed using Stata v12.1 (StataCorp, LP, USE, http://www.stata.com) and statistical significance will be defined as *p* < 0.05, unless stated otherwise.

In the sub-study, the linear regression of log^57^A^t^ (^57^A^t^ = abundance at time t) against time will be calculated for each subject belonging to the three different groups for the period of Day 0 to Day 84 (with a midpoint sample at day 49). The slope (k_abs_) of the regression reflects the absorption of iron per unit of time. The difference in the slopes between the groups will be equivalent to the average iron absorption over time in each group (k_abs_ in groups A, B, and C, respectively).

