The assumption of homogenous labelling will be assessed by testing the linearity of the slope between Days 0, 49 and 84. In each subject, k_abs,i_ will be calculated from the slope of the isotopic ratio decrease over the intervention period. k_abs,c_ will also be calculated for the control period (Day 84 and 168). k_abs_ will be modelled using linear mixed models with time (intervention and control period) and treatment as fixed factors and subjects ID as random factors. The time treatment interaction on k_abs_ will be assessed. A similar but separate analysis will be conducted on the total amount of iron absorbed, which will be estimated from the k_abs_ value in each subject, and the group and time effect will be modelled with linear mixed models. The models will be compared to the standard treatment of supplementation with 12 mg iron/day universal.

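### Sub-study: the two k_abs slopes share the Day 84 sample, and a subject random factor cannot represent the negative correlation this may cause, so the period contrast and the time-by-treatment test could be too liberal

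*Protocol article*

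**What the plan says.** All statements are in the protocol article.

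- **Statistical analysis, intervention slope.** It is a regression of log isotope abundance on time, "for the period of Day 0 to Day 84 (with a midpoint sample at day 49".
- **Statistical analysis, control slope.** k_abs,c "will also be calculated for the control period (Day 84 and 168".
- **Statistical analysis, model.** Both values per child go into "linear mixed models with time (intervention and control period) and treatment as fixed factors and subjects ID as random factors". The article adds: "The time treatment interaction on k_abs_ will be assessed". A separate analysis of the same kind is planned for total iron absorbed, estimated from k_abs.
- **Sample size.** For the two periods: "Twenty subjects per group are required to resolve a difference in absorbed iron of 0.080 mg/d between the control and intervention period". The variability and the test assumed for that figure are given as "based on a SD of 0.13 mg/d (paired t-test". For arms: "The between group difference that we estimate being able to resolve is 0.12 mg/d absorbed iron (unpaired *t*-test". Allowing for attrition, "30 subjects per group will be recruited".
- **Study objectives.** Secondary objective iii is overall absorption during the 12 supplementation weeks in the three arms.

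**The concern.** The Day 84 sample is the last point of the intervention slope and the first point of the control slope. An error in it tilts one slope up and the other down, which pushes the within-child correlation of the two slopes towards negative values.

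With two values per child, a subject random factor amounts to a common correlation that must be zero or positive. If the net correlation is negative, the fit stops at the boundary: the subject variance is set to zero and the slopes are analysed as if they came from different children. The variance of a within-child difference is then understated. Two tests depend on that variance: the intervention-versus-control contrast and the time-by-treatment interaction. At stake are false claims that absorption changed between periods, or changed differently by arm.

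**Working it through.** **1. The plan's own figures.** Assume two-sided 5 % and 80 % power, which the sub-study text does not state. For the paired comparison, n = (0.13 x (1.960 + 0.842) / 0.080)^2 = 20.7, so 21 against the stated 20. (An exact paired t-test needs 23; its power at 20 is 74 %.) For the unpaired comparison with 20 per group and SD 0.13, the resolvable difference is 0.118, which rounds to the stated 0.12 mg/d. The sizing therefore reproduces closely, and pairing was intended for the period comparison.

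**2. Error correlation of the two slopes.** Take equal, independent error variance s^2 per sample (an assumption).
- Days 0, 49, 84: mean 44.33; deviations -44.33, 4.67, 39.67; Sxx = 3560.7.
- Var(k_abs,i) = s^2 / 3560.7 = 2.81e-4 s^2.
- Var(k_abs,c) = 2 s^2 / 84^2 = 2.83e-4 s^2.
- Cov = -(39.67 / 3560.7) x (1 / 84) s^2 = -1.33e-4 s^2.
- Correlation = -1.33 / sqrt(2.81 x 2.83) = -0.47.

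**3. If the slopes are treated as independent.** The true variance of the difference is (2.81 + 2.83 + 2 x 1.33) / (2.81 + 2.83) = 1.47 times the model's. The model's standard error is sqrt(1 / 1.47) = 0.825 of the correct one. The two-sided error is P(|Z| > 1.96 x 0.825) = 10.6 %.

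**4. When the net correlation is negative.** Let r be the between-child variance of true slopes divided by the slope error variance, and rho the correlation of true slopes across periods. The net correlation is positive when r x rho > 0.47:
- rho = 1: r > 0.47, an error share below 1 / 1.47 = 68 % of slope variance;
- rho = 0.5: r > 0.94, an error share below 1 / 1.94 = 52 %;
- rho = 0: never.

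**5. Size of the effect.** Simulation with 20 children in each of three arms, no true effect, 20,000 trials per row, a REML random-intercept fit with subject variance held at or above zero, and Wald tests at 5 %. The period contrast is averaged over arms.

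| Error share | rho | Net correlation | Subject variance estimated as 0 | Period contrast | Interaction |
|---|---|---|---|---|---|
| 100 % | - | -0.47 | 100 % | 10.7 % | 13.6 % |
| 80 % | 1 | -0.18 | 91 % | 7.7 % | 8.0 % |
| 50 % | 0 | -0.24 | 96 % | 7.9 % | 9.5 % |
| 25 % | 0 | -0.12 | 81 % | 7.0 % | 7.3 % |
| 50 % | 0.5 | +0.02 | 45 % | 6.0 % | 6.3 % |
| 25 % | 0.5 | +0.26 | 3 % | 5.6 % | 5.9 % |
| 50 % | 1 | +0.27 | 2 % | 5.3 % | 5.4 % |

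Over the same rows, a t-test and an F test on within-child differences gave 4.7-5.2 % and 4.6-5.1 %. Results with 30 per arm were nearly identical. A second simulation, with a within-arm contrast and an F test for the interaction, gave 10.6-10.8 % and 12.5-13.2 % in the all-error case.

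**6. What is not affected.** The arm comparison of the Day 0-84 slope uses one slope per child. Under the stated model its error was 5.0-5.3 % (z) or 4.8-5.1 % (t) in nine scenarios, including pure error. The reason is that at the boundary the model's variance is the average of the two slope variances, and their error parts (2.81e-4 and 2.83e-4) are almost equal.

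**The case against.** Much of the case for leaving the plan alone stands.

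- **The harm is conditional.** At any clearly positive net correlation, the stated model gives the same test as the paired analysis. A random subject factor is a conventional choice, and it does not in itself contradict the paired sizing. A reader might infer that sharing Day 84 is enough to make the model fail. It is not: error covariance must outweigh, or nearly cancel, the covariance of true slopes.
- **One numerical clue points to a positive correlation.** SD 0.13 reproduces both sizing figures. If it is the SD of a difference in the paired case and of a single period in the unpaired case, then 2 x (1 - correlation) = 1 and the correlation is +0.5, where the model is sound. However, the article does not say which SD is meant, and the figure is for absorbed iron, not k_abs. Two unquantified statements point the other way. The Sample size section describes k_abs as free of Hb, body weight and iron status, child-level sources that could have kept the correlation positive. The Background describes iron accumulation as inducing hepcidin in a negative feedback. None of this settles the sign.
- **Objective iii is not at risk through its direct comparison.** A reader might take the inflation to reach every claim about absorption by arm. It reaches only arm differences in the change between periods.
- **Absorbed iron is a different outcome.** The article attributes most of its variability to Hb, body weight and iron status, which are probably similar in adjacent periods. The all-error case does not carry over, and no inflation has been shown there.
- **Covariance structure is often left to the analysis plan.** This is fair as to detail, and the article does not exclude a residual correlation. It does name a model, though, and that model as worded permits only zero or positive correlation.

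**Conclusion.** The point holds as a conditional weakness of a stated method, of minor severity. The shared Day 84 sample and the error correlation of about -0.47 follow from the sampling days, given equal, independent error per sample. If measurement error is a large part of slope variance, or true slopes correlate weakly across periods, the standard errors of the period contrast and the time-by-treatment test could be up to about 17 % too small (1 - 0.825). In the worst case, with no between-child variance in true slopes, type I error is about 10-11 % and 13 %. It is about 5 % once the net correlation is clearly positive. The article gives neither the error share nor the within-child correlation, so where the trial falls in this range is unknown. The primary haemoglobin comparison and the between-arm comparison of the Day 0-84 slope are not inflated.

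**What to change.** In the sub-study part of Statistical analysis, replace the subject random factor in the k_abs model with an unstructured 2x2 within-child covariance for the intervention and control periods. This allows a negative correlation and unequal variances. For complete pairs, an equivalent route is to analyse k_abs,i - k_abs,c: a paired t-test within each arm, matching the sizing, and a one-way comparison of the differences between arms for the time-by-treatment test. The same wording can serve the absorbed-iron model, although a need for it there is not established.

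The cost is one line of text, with no extra samples or children. When the correlation is negative, intervals widen (by up to 1 / 0.825 = 1.21) and error degrees of freedom fall. With 60 children in three arms, the interaction test has 60 - 3 = 57, against 2 x 57 = 114 when the slopes are treated as independent. Where the correlation is clearly positive and pairs are complete, results are essentially unchanged.

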## Discussion

Prevalence of anaemia is > 50 % and remains a major public health problem in young children in The Gambia. Combating anaemia due to iron deficiency is a challenge due to the potential negative side effects of iron when given to people with infections, as is common in The Gambia. The present randomised controlled trial of screen-and-treat aims to minimise unnecessary exposure to iron. This will decrease the potential adverse effects of giving iron at a time when the body can’t utilise it and will allow maximising the absorption and utilisation of iron when it is most needed. If a screen-and-treat approach using a hepcidin cut-off to define ‘ready and safe to give iron’ is non-inferior to universal supplementation, then this approach could be used in every health centre. We hypothesise that the development of a point of care test, which would immediately tell the nurse/physician if the person is ready to receive iron, would make iron administration more targeted and safer.

## Abbreviations

AGP: Alpha 1-acid glycoprotein
CRP: C-reactive protein
Hb: Haemoglobin
ID: Iron deficiency
IDA: Iron deficiency anaemia
MNP: Micronutrient powders
MRC: Medical Research Council
RBC: Red blood cell
RDT: Rapid diagnostic test
SD: Standard deviation
sTfR: soluble transferrin receptor
TSAT: transferrin saturation
WHO: World Health Organization
